### Study objectives

As complex interventions, social accountability interventions have several interacting components where it is difficult to identify ‘the active ingredients’ producing effects, and a range of outcomes is possible
^24^. The Medical Research Council’s (MRC) guidance on evaluating complex interventions recommends evaluating outcomes alongside process
^25^. To inform policy and practice, we need to know whether interventions ‘worked’ or not, but also how they were implemented, their causal mechanisms and how effects differed from one context to another.

The CaPSAI Project examines both the impact and processes of a social accountability intervention in the context of FP/C programming. Specifically, it aims to measure the effect of the intervention on contraceptive uptake and use. It also aims to understand the mechanisms and contextual factors that influence and generate these effects.

Two objectives were identified:

1. To develop more responsive quantitative measures for social accountability as well as show the relationship between social accountability and uptake of contraceptives and use and other FP/C behaviors;2. To describe and examine how social accountability interventions are implemented and operationalized with a focus on understanding behaviors, decision-making processes, and the barriers and facilitators of change, with a view to generalizability.

To capture changes in contraceptive uptake and use, two designs are used:

i. 
*Contraceptive uptake*. A quasi-experimental pre-test post-test study, using a facility audit in both intervention and control facilities to determine the actual number of new users of contraception amongst women 15–49 in study catchment areas.ii. 
*Contraceptive use*. A cohort of women who are new users of contraception, using standardized interview questions across both intervention and control facilities are tracked to measure changes in behaviors around contraceptive.

To measure the effects of the social accountability intervention, two additional designs were also used:

iii. 
*Social accountability outcomes*. An evaluation of the intermediary outcomes related to the social accountability intervention, using a questionnaire of psychometric scales among health care providers and service users in the intervention facilities only. We also assess the feasibility, acceptability, and validity of the instrument.iv. 

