In each country, districts were pre-selected based on similar cultural, religious and socio-economic context, as well as presence of enough health facility offering FP/C services. Data on at least 20 facilities in the pre-selected districts, where there are no social accountability intervention in FP/C currently taking place, were gathered. From the initial list, eight intervention and eight control facilities were selected based on the following criteria: provision of contraceptive services; availability of the following methods: a barrier method, a short and long-acting method, emergency contraception, and at least referral for permanent methods in districts; no social accountability programs in FP/C currently underway. Criteria that include facility type and level, average number of service users and number of new users, will be used to match the study and control facilities.

3
Study design

The study design contains two parts: capturing changes in contraceptive uptake and use (i and ii) and evaluating the effects of the social accountability intervention (iii and iv). The overview of the study design is summarized in
Table 3.

**Table 3. T3:** Study overview table.

Data gathering activity	Facility audit	Cohort study	Cross sectional survey	Process evaluation
	Changes in contraceptive uptake and use		Effects of the social accountability process	
*Outcomes*	Contraceptive uptake (new users)	Contraceptive use (method discontinuation, continuation and switching)	Social accountability intermediate outcomes (service user and health provider empowerment; expansion of negotiated space)	Dose, reach and fidelity: Process evaluation and context mapping
**Participants**	Health facilities providing FP/C services	A cohort of new users	Health Care Providers, New and continuing users of facilities women accessing FP/C services in intervention facilities	Community and district participants and staff at key program/ implementation events N.B. The context mapping activity will be undertaken in both intervention and control sites.
**Study size**	Eight intervention and eight control facilities	Estimated 800 women over eight study facilities per arm	Health care professionals (two per site) and 750 women	Four process evaluations per country tracking between 8–12 intervention related events each

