**Setting**	Intervention and control facilities	Intervention and control facilities	Intervention facilities	Intervention facilities N.B. The context mapping activity will be undertaken in both intervention and control sites (three interviews per district).
**Timing** *(N.B. Month 1–4* *was for preparing* *the study)*	Baseline: Month 5 Interim: Month 17 End-line: Month 29	Intake: Month 10–12 Check-up: Month 16–18 Follow up: Month 22–24	Pre-test: Month 5 Post-test: Month 17	8–12 data points tied to key events in the intervention facilities between Month 6 and Month 18. Eight events at four intervention facilities per country.
**Data sources**	Facility audit of FP/C facilities	Prospective cohort follow-up of new users	Cross sectional survey using a questionnaire of psychometric scales with women accessing FP/C and health care providers in intervention sites	Context mapping (three per district for both the intervention and control sites) In-depth interviews (three per observation) Observations (8–12 per process evaluation site) Document review

i. 
*Capturing changes in contraceptive uptake:* A quasi-experimental study utilizing an interrupted time series design with a control group (ITS-CG) is conducted to determine the actual number of new users of contraception amongst women 15–49 years old in eight intervention and eight control facilities per country. New users are defined as: never used an FP/C method (new acceptors); are switching from a traditional to a modern FP/C method (additional users); or are re-starting an FP/C method after a period of not using it for at least six months (additional users). The facility is the sampling unit.Contraceptive uptake in both the intervention and control arms is measured by comparing the level changes and trends over time during the study period. The numerator of the rate is measured using the facility audits provided by the intervention and control facilities, while the denominator of the rate, measured at the community level, is the number of women of reproductive age in the catchment area for the facility. The facility catchment area definitions used are those provided by Ghana Health Service in Ghana and the Ministry of Health in Tanzania. The catchment area study population size is collected from official statistics calculated on a yearly basis and, based on trend analysis, is expected to remain roughly constant throughout the study duration.ii. 

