*Capturing changes in contraceptive use*: A cohort of women, 15 to 49 years of age, who are new users of contraception and who are accessing FP/C services at the study facilities are tracked across both intervention and control facilities to measure changes in behaviors around contraceptive use such as method continuation, switching, contraceptive decision making, and client satisfaction. Method contraception discontinuation rate (first use) is estimated using a prospective cohort study design. The outcome of interest is time from starting modern contraceptive method use until when use is discontinued.Contraceptive method continuation (proportion of women in a cohort using the same contraceptive method after one year) and contraceptive switching (proportion of women in a cohort changing method within one year of initiation, out of those using any method at baseline/proportion of women, because they were not satisfied with the previous one) are measured.iii. 
*Evaluating effects of the social accountability process:* To capture the intermediate outcomes outlined in the ToC (see
Figure 1), such as empowerment of women and health providers and expansion of negotiated spaces, a cross-sectional survey using accountability-related psychometric scales is conducted at pre- and post-intervention phases. One survey is conducted with women accessing FP/C services in health facilities in the catchment areas where the social accountability intervention is being implemented. Another survey is conducted with health workers providing FP/C services in health facilities in the catchment areas where the social accountability intervention is being implemented.iv. 

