*Contraceptive use:* The discontinuation rate, being a time-to-event outcome and involving censoring, necessitates the use of sample size estimation methods for survival data. Different sample size estimates were computed for values of hazard ratio (intervention vs control) of 0.5, 0.6 and 0.7, and given values of the proportion of discontinuing use of modern contraception by end of the first year, in the control arm range from 30% to 60%. Sample size estimates were obtained using a Type I error at 5% level, accrual time of 0.01 years, and an exponential loss to follow-up of 20% that would enable a two-sided Logrank test to achieve 80% statistical power to detect the difference in discontinuation rates by the end of one year of follow-up. The final sample size was also adjusted for clustering
^40^ due to the intervention being offered at cluster level. Assuming an intra-class correlation of 0.05 and an average cluster size of 20 first users of modern contraception, resulting in a design effect of 2.0, the final sample size was doubled. The sample is estimated to be 800 women across five to eight study facilities per arm. The total sample is estimated at 1600 women distributed depending on the size of the facilities in the intervention and control arms in each country.iii. 
*Social accountability intermediate outcomes:* In intervention facilities, health care professionals providing FP/C services (two per site at pre- and at post-intervention) and 750 women aged 15 to 49 years accessing FP/C services are interviewed pre- and post- intervention over an 18-month period. Sampling for the service users survey was calculated using
*a priori* sample size calculation with the ratio of ten subjects per item ratio and guidance of more than 500 which equals a very good sample for validation
^11,
41^. The calculation is based on 75 items.iv. 

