^42^ is conducted with service users at the facilities receiving the intervention at pre- (before step 1 of the intervention) and post-intervention (starting after completion of step 8) and completed within three months. The study uses the CARE’s Women’s VOICES tool to measure these outcomes in sexual, reproductive and maternal health programs, adapted to assess FP/C programs
^47^. Some measures were adapted and new measures were added; these were field tested but did not undergo formative research. The service user survey is conducted using a tablet-based questionnaire to capture real-time data using OpenClinica Participate. Data are checked during data entry and potential data errors and inconsistencies are notified and resolved immediately. The health provider survey is conducted with paper-based CRF and collected data are entered at each country using a customized web-based EDC system using OpenClinica Enterprise platform. The screening and enrolment logs are kept at the sites by the local study team.iv. 
*Process evaluation:* NONs and IDIs as part of the process evaluation are conducted during key events related to each of the eight intervention steps in four of the eight intervention facilities in each country.The NON instrument collects data on activities related to the CaPSAI and allow the capture of a broader picture of the intervention in action and the roles taken by citizens and health services actors in the social accountability process. The IDIs collect experiential data from key actors in the social accountability intervention including citizens, health care providers, and duty bearers (see ContextMapping_ProcessEvaluation,
*Extended data*)
^42^. They are asked about their experience of the CaPSAI intervention, what they believe its impacts have been and their experience of intervention-related events. Document review is done as needed in all the eight intervention facilities.

6
Data analysis

The four main outcomes of interest will be analyzed in the following manner:

i. 

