*Social accountability intermediate outcomes:* Demographic data are collected and will be analyzed for representativeness. We will use difference-in-difference (DiD) and local average treatment effect (LATE) estimates to evaluate changes in social accountability intermediate outcomes at pre and post-intervention periods. The outcomes include knowledge and awareness of rights, decision making, self-efficacy, political capabilities and collective efficacy among women and health providers. For the validity of the service users scale, an analysis of the distribution of responses for individual items will be conducted and those with no variability will be removed. A reliability analysis will follow on each proposed scale, with items removed in accordance with standard procedure. The distribution of overall and dimension scores will be analyzed by calculating mean scores and standard deviations (SD). Floor and ceiling effect will be assessed. To determine internal consistency, Cronbach’s Alpha analysis will be conducted with the use of standard thresholds of 0.60 for acceptable reliability and 0.70 to be good or high reliability. Re-test will be assessed using intra-class correlation coefficient. We will be assessing the feasibility and acceptability of the instrument by assessing the time taken to complete the questionnaire and ease of use through analysis of the completion rate and range of missing answers.iv. 

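### Difference-in-difference and LATE are planned for a survey that is run in intervention facilities only, so neither can be estimated as the plan stands

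*Protocol article*

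**What the plan says.** The analysis is in the Protocol article, Study design and methods, 6 Data analysis, item iii: "We will use difference-in-difference (DiD) and local average treatment effect (LATE) estimates to evaluate changes in social accountability intermediate outcomes". The outcomes are scale scores such as knowledge of rights, self-efficacy and collective efficacy, in women and in health providers, compared between the pre- and post-intervention surveys.

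The article describes who is surveyed in several places:

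- Study objectives, item iii: "using a questionnaire of psychometric scales among health care providers and service users in the intervention facilities only".
- Table 3, participants: "New and continuing users of facilities women accessing FP/C services in intervention facilities".
- Table 3, data sources: "with women accessing FP/C and health care providers in intervention sites".
- 3 Study design, item iii: "One survey is conducted with women accessing FP/C services in health facilities in the catchment areas where the social accountability intervention is being implemented". The provider survey is placed in the same catchment areas.
- 4 Sample size, item iii, which opens by restricting the sample to intervention facilities: "750 women aged 15 to 49 years accessing FP/C services are interviewed pre- and post- intervention over an 18-month period", plus two providers per site at each wave.
- 5 Data collection, item iii: the survey "is conducted with service users at the facilities receiving the intervention at pre- (before step 1 of the intervention", and again after step 8.

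In the setting row of Table 3, the facility audit and the cohort are assigned to both kinds of facility and the survey to intervention facilities alone. The restriction is therefore part of the design and not a slip in one sentence.

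**The concern.** Both named estimators are defined by a contrast that this survey does not contain. Difference-in-difference subtracts the change seen in an untreated group. LATE rescales an outcome contrast between levels of an instrument, usually assignment, by the matching contrast in treatment received. Here there are two cross-sections from the same intervention facilities, with no untreated group and no variation in assignment.

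Followed literally, the analysis cannot be carried out. The practical risk is that a single-group pre-post change is reported under one of these names. Readers would then take it as adjusted for secular change, when other family planning programmes, media activity, staff turnover or a shift in the mix of respondents could have produced it. The article presents this survey as one of the designs for measuring the effects of the intervention, and its outcomes are the intermediate links in the theory of change. A mislabelled estimate would therefore bear on the account of how the intervention works.

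**Working it through.** **1. The plan's own figure.** The survey size in 4 Sample size, item iii, rests on ten subjects per item and 75 items: 10 × 75 = 750 women. This reproduces exactly. It is a rule for validating scales and was not derived from a comparison between arms.

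**2. Difference-in-difference.** Let a = 1 for intervention and 0 for control, and t = 0 before and 1 after. The model is

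E(Y) = b0 + b1·a + b2·t + b3·a·t,

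and b3 = (Y₁,post − Y₁,pre) − (Y₀,post − Y₀,pre).

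The distinct design rows (intercept, a, t, a·t) are:

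| Cell | Row | Collected? |
|---|---|---|
| Intervention, pre | 1, 1, 0, 0 | yes |
| Intervention, post | 1, 1, 1, 1 | yes |
| Control, pre | 1, 0, 0, 0 | no |
| Control, post | 1, 0, 1, 0 | no |

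With the two collected rows the rank is 2 of 4, and the interaction contrast (0, 0, 0, 1) does not lie in the row space, so b3 is not estimable. With all four rows the rank is 4 of 4 and b3 is estimable. Surveying more women in intervention facilities does not change this.

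**3. LATE.** With assignment Z and treatment received D, the Wald form is

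[E(Y | Z=1) − E(Y | Z=0)] / [E(D | Z=1) − E(D | Z=0)], equivalently Cov(Y, Z) / Cov(D, Z).

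Every respondent comes from an intervention facility, so Z = 1 throughout, Var(Z) = 0 and the ratio is 0/0. The article names no other instrument.

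**4. What is identified.** Two cell means give

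Y₁,post − Y₁,pre = intervention effect + secular change S.

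Read as an effect, the pre-post change has bias S, and the survey holds no data from which to estimate S. Table 3 puts the surveys at Months 5 and 17, so S accumulates over 17 − 5 = 12 months. The sample-size text speaks of an 18-month period, and the two statements should be reconciled. The argument is the same for either interval.

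**5. Could control data still be added?** If control facilities were surveyed at the same size (an assumption), each wave would have 2 × 750 = 1,500 women. The pre-test, however, precedes step 1, and Study status says baseline collection began in March 2018. A control pre-test cannot be obtained retrospectively.

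**The case against.** The strongest reply is that a comparison group need not be the control arm. Exposed and unexposed women within intervention facilities might be contrasted, and the survey questionnaire, which is in the extended data, may record exposure. This does not rescue difference-in-difference. The article defines no such contrast and mentions an exposure question only for the cohort instruments. The pre-test precedes step 1, so nobody is exposed at that wave. The waves are cross-sections with no linkage of women described, so baseline exposed and unexposed groups cannot be formed from individual exposure.

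A second reply is that survey period could act as the instrument for LATE. That ratio can be computed. If a proportion p of women are exposed at the post-test and none at the pre-test, it equals (p·τ + S)/p = τ + S/p, where τ is the effect in exposed women. Since p is at most 1, the bias is at least as large as S. The approach is valid only if there is no secular change, which is the point at issue.

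A third reply is that the article acknowledges the problem. Study limitations concedes that attribution is difficult, and context mapping is planned in both intervention and control districts. Both points are fair, and they lower the risk that secular influences go unnoticed. The mapping is qualitative, though, and cannot supply the missing cells.

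Some of the objection stands. The affected outcomes are intermediate. Uptake and use have control facilities and are untouched, as is the psychometric work that takes up most of the same analysis paragraph. Objective 1 rests only partly on this survey. A comparison of facilities by implementation dose is also possible, so a pre-post change is not literally the only thing that can be computed. Such a comparison is not specified, dose is not randomised, and it would not be a LATE.

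**Conclusion.** The concern holds. The article commits to two estimators whose comparison group or instrument is excluded by every description of the survey. Two of the four cells needed for difference-in-difference do not exist (rank 2 of 4), and assignment has zero variance for LATE. The arm-level quantity that can be estimated is an uncontrolled pre-post change, biased as an effect estimate by the full secular change, whose size the survey cannot reveal.

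This rests on the survey being run as described, in intervention facilities only and as unlinked cross-sections. It is a contradiction within the article and not detail deferred to an analysis plan, because no plan can supply control data that are not collected. It should be corrected before the analysis is run.

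**What to change.** Remove difference-in-difference and LATE from 6 Data analysis, item iii. In their place:

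- State the estimand as the pre-post change in each scale score within intervention facilities.
- For women, adjust for respondent mix, use fixed or mixed facility effects, and give cluster-robust intervals with a small-sample correction, since there are only eight intervention facilities per country.
- Treat providers separately. Two per site in eight facilities is 2 × 8 = 16 per country per wave, which supports little beyond description.
- Report the result as change over time, say that secular change cannot be separated from an intervention effect, and carry this into the conclusions drawn about the theory of change.
- If change is also compared by recorded local exposure or dose, define the measure beforehand and label the analysis exploratory and associational. Intensive process data cover only four of the eight intervention facilities in each country, with documents alone for the rest.
- Reconcile the 12-month spacing in Table 3 with the 18-month period in the sample-size text.

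The cost is a rewording of the analysis section and a weaker causal claim for the intermediate outcomes. No new data are needed.

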### Study status

Baseline data collection was initiated in March 2018 and endline data collection will be conducted in March to April 2020.

## Discussion

### Measuring impact of a process – ITS analysis

Contraceptive uptake is an outcome of interest and will be evaluated using ITS analysis. ITS study design is increasingly being used to evaluate public health interventions that are introduced over a defined time period and target population-level health outcomes
^48^. Randomized control trials (RCTs) are considered as the gold standard in studying causality as well as being efficient in terms of minimizing the risk of bias, but they are not always feasible due to ethical or practical reasons. ITS-CG design is considered the next-best design after RCT.

